## Abstract

**Background:**

Cystic fibrosis (CF) is a genetic disorder, which is caused by the CFTR protein defects. Along with CFTR dysfunction, inflammation plays a key role in the disease outcomes. Inflammation may develop due to the internal dysfunction of the CFTR protein or external factors. Curcumin affects the CFTR protein function primarily as a corrector and potentiator and secondary as an anti-inflammatory and antimicrobial agent. The present study aims to assess the impact of nano-curcumin on clinical and inflammatory markers in children with CF.

**Methods:**

This prospective, double blind control trial will be conducted at the Akbar Children’s Hospital in Mashhad, Iran. Children with CF will be enrolled based on the eligibility criteria. Placebo and curcumin with the maximum dose of 80 mg considering the body surface of the patients will be administrated for 3 months. The primary outcome is to evaluate inflammation based on serum interleukin-6, interleukin-10, and hs-CRP, stool calprotectin, and neutrophil count of nasopharyngeal swab. The secondary outcome involved clinical assessment via spirometry, anthropometrics, and quality of life. They will be assessed before and after 3 months.

**Discussion:**

Due to the multifarious effects of curcumin on CF disease, it could be proposed as a nutritional strategy in the treatment of cystic fibrosis.

**Trial registration:**

Iranian Registry of Clinical Trials IRCT20200705048018N1. Registered on July 10, 2020.

**Supplementary Information:**

The online version contains supplementary material available at 10.1186/s13063-021-05224-6.

## Administrative information

The order of the items has been modified to group similar items (see http://www.equator-network.org/reporting-guidelines/spirit-2013-statement-defining-standard-protocol-items-for-clinical-trials/).

## Introduction

### Background and rationale {6a}

Cystic fibrosis (CF) is a common, life-shortening, autosomal recessive, genetic disorder in Caucasian populations. The disease prognosis has improved in recent decades with the advances in the treatment procedures, and the mortality rate has decreased by 2% annually. The median age of survival in the male and female patients with CF has been reported to be 65 and 56 years, respectively [1]. Inflammation plays a critical role in CF lung pathology and disease progression. The abnormal function of cystic fibrosis transmembrane conductance regulator (CFTR) alters the chloride ion transport in the epithelial cells, hence leading to the dehydration of the airway surface liquid. This condition causes the secreted mucin to thicken and contribute to airway obstruction, thereby predisposing the patients to infection. This is considered to be the leading cause to trigger inflammation [2]. The dysregulation of the pro-inflammatory mediators secondary to the innate and adaptive immune dysfunction in CF patients is another cause of excessive inflammation. It remains unclear whether the intrinsic effects of mutant CFTR on the immune system are the major cause of inflammation or exposure to the CF airway infection and inflammatory environment could exert extrinsic effects toward this phenomenal [3, 4]. With the advent of new modified CFTR protein drugs such as ivacaftor, lumacaftor, tezacaftor, a significant impact has been observed on the treatment of patients. Ivacaftor and tezacaftor act as the potentiator through enabling the opening chloride channel, while lumacaftor acts as the corrector through increasing the trafficking of the CFTR proteins to the outer cell membrane [5, 6]. Although these drugs could reduce airway inflammation, they cannot eliminate it completely [7]. On the other hand, these drugs affect specific mutations and do not cover all patients with various mutations [7]. Therefore, anti-inflammatory treatments are an inevitable therapy for CF patients. Curcumin is the main ingredient in turmeric with a substantial impact on the reduction of inflammatory factors [8, 9]. The first study published by Egan et al. demonstrated that curcumin induced accumulation of complex-glycosylated F508 CFTR and increased cell surface density [10] Curcumin as a sarcoplasmic/endoplasmic reticulum calcium (SERCA) pump inhibitor could increase the appearance of functional DF508 CFTR on the plasma membrane cells [10]. On the other hand, curcumin suppressed the endogenous calreticulin mRNA transcription, which is a chaperone protein could bind to the mutant CTFR protein and carry this complex to the ER. so that CFTR protein can be stabilized on the cell membrane [11].

Potentiation function of curcumin has been reviewed and confirmed in a number of studies. Curcumin can react as a potentiator that repairs sub activation of CFTR protein activity and also accelerates CFTR protein activity which has been increased by other CFTR modulation in mutations such as S1251N, G551D, and F508del [12]. Curcumin can increase G551D-CFTR opening channel and its activity on its own, or when it is added to the channel that is further affected by genistein. Thus, these neutral components are suggested to have different mechanisms as potentiations of channels [13]. Similarly, curcumin stimulates channels which lack NBD2 due to deletion of G551D CFTR mutants, where effect is persistent and irreversible [14].

W1282X is another common CF mutation which reduces CFTR function by reduction of steady state levels of CFTR mRNA and also lowering the channel activity due to the defect of the second cytosolic nucleotide binding domain (NBD2) that is a surface that bind to ATP molecules [15–17]. According to several studies, curcumin stimulated W1282X-CFTR after adding a saturating dose of VX-770; thus, it increased the rate of channel opening. In addition, both curcumin and VX-770 are acting as allosteric modulators since they stimulate activity of the CFTR channel without ATP binding, but with different mechanisms [18].

According to the literature, curcumin can reduce inflammation through several mechanisms. Inflammation has a significant role in the outcome of cystic fibrosis patients. Studies have shown an extensive inflammation on pulmonary, gastrointestinal, and systemic levels in CF patients.

Mucus plugging is suitable for microorganism growth and neutrophilic inflammation as it has many nutrients. It is believed that delayed neutrophil apoptosis and long lifespan of neutrophils could increase the levels of neutrophil extracellular traps (NETs); thus, inflammation is induced [19]. Moreover, differentiation of monocyte in to macrophage and division into M1 or M2 phenotype are unsuccessful in CF patients, and hence, it does not produce IL-13Rα1 on the surface. This impaired process contributes to excessive inflammation in CF lung disease [20]. Last but not least, the highest number of Th17 cells is present in the CF lung. Th17 cells produce both IL-8 and IL-17 and promote neutrophil accumulation. These T cells are activated by IL-6, IL-23, and TGF-β and suppressed by active T regulatory-lymphocytes (Treg). Otherwise, a CFTR abnormality or an unknown imbalance between Th17 cells and Treg can induce inflammation by neutrophil recruitment [2].

Anti-bacterial effect of curcumin has also been considered in several studies. Toll-like receptor-2(TLR2) is a receptor of pathogenic bacteria like *Staphylococcus aureus* peptidoglycan (PGN), is found in epithelial cell and has a key role in recognizing the infected pathogen, increases inflammatory cytokines as a result, and is upregulated in CF patients. Cystic fibrosis patients are prone to infection since absence of CFTR protein causes demethylation of DNA at the specific CpG sites which overlaps a minimal region to maintain activity of TLR2 promoter [21]. Curcumin can degrade specificity protein 1 (SP1) via oxidative and proteasome degradation pathways. This factor is essential for upregulation of TLR2 expression. Consequently, curcumin decreases basal expression of TLR2 [22]. Finally, curcumin has been proved to have a significant effect on suppressing the growth of *P. aeruginosa* on biofilm optical densities, although the MIC (minimum bacterial concentration) which is needed for growth suppression is higher than other usual *P. aeruginosa* treatments such as imipenem or tobramycin [23].

The above evidence suggests that curcumin has potential effects on CF patients.

It must be considered that curcumin is soluble in water and has a short half-life and low bioavailability. Various products have been obtained for the improvement of bioavailability through increasing the absorption rate from the gastrointestinal tract and reducing the liver metabolism [24–26].

The present study aimed to evaluate the effects of nano-curcumin on CF patients in order to achieve the intrinsic and extrinsic effects of curcumin on the inflammatory process in these patients.

### Objectives {7}

The present study aimed to evaluate the effects of nano-curcumin on CF patients in order to achieve the intrinsic and extrinsic effects of curcumin on the inflammatory process in these patients.

### Trial design {8}

This is a prospective, single center, double-blind, parallel, randomized placebo-controlled clinical trial. The study protocol was written following the standard Protocol Items Recommendation for Interventional Trials (SPIRIT) Checklist (Table 1).

**Table 1 Tab1:**
[figure not shown]
Schedule of enrolment, intervention, and assessment based in the Standard Protocol Items Recommendations for Interventional Trials (SPIRIT) guidelines

## Methods: participants, interventions, and outcomes

### Study setting {9}

The study population will consist of the patients with known CF referring to the Cystic Fibrosis Clinic at Akbar Children’s Hospital, Mashhad, Iran.

### Eligibility criteria {10}

#### Inclusion criteria

The inclusion criteria of the study are as follows: (1) one or more typical phenotypic features of CF and a minimum of an elevated sweat chloride concentration on two/more occasions or two mutations known to cause CF on separate alleles; (2) age of 5–18 years; (3) pulmonary and gastrointestinal involvement; (4) ability to perform spirometry maneuvers and the minimum FEV1 of ≥ 30% compared to the same age, gender, and height in the normal population; (5) the percentage of oxygen saturation based on pulse the oximetry of ≥ 90% at room temperature; and (6) informed consent for participation.

#### Exclusion criteria

The exclusion criteria of the study are (1) cardiovascular, hepatic, and renal failure; (2) celiac disease and rheumatoid arthritis; (3) acute pulmonary exacerbation requiring hospitalization within the past 4 weeks; and (4) acute respiratory tract infection.

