#### Outcomes {12}

The primary outcomes of the current trial are the compared changes in the blood vessel inflammation, nasopharyngeal swab, and fecal samples at baseline with 3 months after the intervention: systemic inflammation by assessing IL-6 as an inflammatory agent, IL-10 as an anti-inflammatory agent, and hs-CRP level in the blood samples, pulmonary inflammation with the neutrophil count, bacterial/viral culture on the nasopharyngeal swab, and gastrointestinal inflammation with the calprotectin level in the fecal samples.

The secondary outcomes are changes in clinical assessment of the pulmonary symptoms via spirometry, anthropometric assessment stand on the BMI Z score, and evaluation of the quality of life using the CFQ from the baseline to 3 months of the intervention.

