#### Participant timeline {13}

Nutritional recommendations will be provided to all the patients and/or their parents and legal guardians stand on the CF requirements and adjustable CREON dosing to the level of dietary fat. In addition, the patients and their parents completed the CFQ depend on age.

Anthropometric measurements (weight and height) will be performed using a digital scale (model: SECA). Body weight will be measured without shoes, and height will be measured in the standing position without shoes with the heels stuck to the wall and the head looking frontwards with the accuracy of 0.5 cm.

The fecal examination will be performed before and after the intervention. Before intervention, fecal sample will be evaluated for bacterial over growth and parasite specially giardia by checking stool PH and trophozoites or cysts of giardia. Any positive result will be treated with antibiotics before stating the trials.

Blood sampling will be performed before and after the intervention. Approximately 5 mL of blood will be collected, immediately centrifuged, with the serum separated from the sediment, and preserved at the minimum of temperature of − 20 °C.

The primary and secondary consequences of the treatment will be investigated before and 3 months after the treatment. The clinical evaluation and follow-up of medication use and side effects will also be carried out via phone call and paying monthly visit to the clinic, and the findings will privately be presented to the patients (Table 2).

**Table 2 Tab2:** Laboratory measurements, equipment, and normal range

Test	Test equipment	Company	Quality control	Normal range
**Hs-CRP**	Biochemical auto analyzer	Pars azmoon	Intra-assay CV: 2.2% Inter-assay CV: 1.1% Linearity (*R*^2^): 0.99 Detection limit: 0.1 mg/lit	Children: up 2.8 mg/L Adult: up to 5 mg/L
**IL-6**	ELISA kit	Demeditec	Intra assay CV: 4.2% Inter assay CV: 4.9% Accuracy: 99% Specificity: 94% Detection limit: 2 pg/ml	Up to 1.8 pg/ml
**IL-10**	ELISA kit	pars gene (Invitrogen)	Intra assay CV < 3% Inter assay CV < 8% Detection limit:2 pg/ml	1.2–7.8 pg/ml
**Calprotectin**	ELISA kit	EUROIMMUN	Intra assay CV: 3.4% Inter assay CV: 6.4% Linearity(*R*^2^): 0.99 Sensitivity: 94.1% Specificity: 95.5% Detection limit:1.9 μg/g	50–120 μg/g: borderline > 120 μg/g: positive
**Nasopharyngeal swab**	URT-S&C (gram-positive, gram negative, pseudomonas)	Variable		Culture: negative WBC count: up to 2–3

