#### Sample size {14}

Due to the lack of clinical trials on the inflammatory effect of nano-curcumin in children with cystic fibrosis, we used HSCRP indices as an effect size. Therefore, the mean ± SD of hs-CRP indices in the curcumin and placebo groups were 5.9 ± 2.57 and 3.6 ± 1.58 respectively [27]. G- power analyzer was applied for calculating sample size between two independent populations with a confidence interval of 95% and power of 80%. By considering 10% dropout and using Deff (deign effect) for stratified sample, a total of 30 samples for each group was calculated. In total, 60 eligible patients with CF are needed to be included for the randomization aspect of this research.

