#### Statistical methods for primary and secondary outcomes {20a}

Data analysis will be performed in SPSS version 16, and data distribution will be evaluated using the Kolmogorov-Smirnov test. Data are expressed as frequencies for the qualitative variables, mean and standard deviation for the normally distributed continuous variables, and median and interquartile range for the other variables. In addition, intergroup differences will be evaluated using paired t-test for the normally distributed continuous variables and Wilcoxon rank-sum test for the other variables. Intragroup differences will be assessed using independent *t* test for the normally distributed continuous variables and Mann-Whitney *U* test for the other variables. The mean changes in the secondary outcomes will also be adjusted for the baseline data and disease severity using the analysis of covariance (ANCOVA). In all the statistical analyses, the *P* value of ≤ 0.05 will be considered significant.

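### The 4-week exacerbation window covers only hospitalized children, so recent outpatient exacerbations may add noise to the primary biomarker changes

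*Protocol article*

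**What the plan says.** Two exclusion criteria in the Protocol article deal with recent respiratory illness (Eligibility criteria {10}, Exclusion criteria). The third excludes "acute pulmonary exacerbation requiring hospitalization within the past 4 weeks". The fourth reads "and (4) acute respiratory tract infection", with no look-back period and no condition on severity or place of treatment.

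Outcomes {12} defines the primary endpoints as changes: "The primary outcomes of the current trial are the compared changes in the blood vessel inflammation, nasopharyngeal swab, and fecal samples at baseline", compared with 3 months later. They include "systemic inflammation by assessing IL-6 as an inflammatory agent, IL-10 as an anti-inflammatory agent, and hs-CRP level in the blood samples", together with nasopharyngeal swab and fecal markers. Participant timeline {13} gives two measurement points: "The primary and secondary consequences of the treatment will be investigated before and 3 months after the treatment". There is one baseline value and one follow-up value per child.

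On analysis, Statistical methods {20a} states: "The mean changes in the secondary outcomes will also be adjusted for the baseline data and disease severity", by ANCOVA. Methods for additional analyses {20b} says that baseline values and severity will be handled by ANCOVA or logistic regression, and does not say for which outcomes.

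**The concern.** Read together, the two criteria let the place of treatment decide entry. A child admitted just under 4 weeks ago is kept out. A child who completed outpatient treatment a few days ago and is no longer acutely infected may be randomised and sampled at once. By setting a 4-week window for admitted children, the protocol accepts that a recent exacerbation makes a child unsuitable for entry, but it does not carry this over to outpatients.

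This matters more than usual here because the primary outcomes are the inflammatory markers themselves. A baseline taken while a marker is still settling produces a fall by month 3 that has nothing to do with the treatment. With one baseline measurement, nothing averages that out. At stake are the precision of the primary comparison and, in a trial of 60, the chance that a few such children land unevenly between the arms.

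**Working it through.** **Inputs from the protocol.** Sample size {14} plans on hs-CRP of "5.9 ± 2.57 and 3.6 ± 1.58 respectively", 80% power, 95% confidence (taken as two-sided 5%), 10% dropout and 30 per group.

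- Pooled SD = √((2.57² + 1.58²)/2) = √4.551 = 2.13 mg/L.
- Planned difference (absolute size) = 5.9 − 3.6 = 2.3 mg/L, so d = 2.3/2.13 = 1.08.
- Evaluable per arm = 30 × 0.9 = 27.

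**The plan's own figure.** A t-test with d = 1.08 and 80% power needs 15 per group, or 15/0.9 → 17 after dropout. Reaching 30 requires a design effect of about 27/15 = 1.8, a value that the protocol does not state. That is a separate matter. For this point it means that 27 evaluable children per arm give 97% power (noncentral t) for the planned difference, so there is slack.

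**Assumptions.** The protocol gives no rate of recent outpatient exacerbations and no size of residual marker rise. Assume that a share f of children enters with an hs-CRP rise r that has gone by month 3, and that the SD of change otherwise equals the planning SD of 2.13.

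**Unadjusted change scores.** The added variance is f(1−f)r². For example, f = 10% and r = 5 give 0.1 × 0.9 × 25 = 2.25, and 2.25/4.551 = 49%.

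| Share f | Rise r (mg/L) | Added variance | Variance of change | Power, planned 2.3 mg/L | Power, effect with 80% at the start (d = 0.778) |
|---|---|---|---|---|---|
| none | – | 0 | – | 97% | 80% |
| 5% | 3 | 0.43 | +9% | 96% | 76% |
| 10% | 3 | 0.81 | +18% | 95% | 73% |
| 10% | 5 | 2.25 | +49% | 89% | 63% |
| 20% | 5 | 4.00 | +88% | 81% | 53% |

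Power for the planned difference drops below 80% only when the variance rises to about 1.9 times its planned value.

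**Baseline-adjusted analysis.** Assume equal SDs at both visits. An SD of change of 2.13 then fits a per-visit SD σ of 2.13 and a correlation ρ of 0.5, since 2σ²(1−ρ) = σ². The rise inflates only the baseline value. With V = f(1−f)r², the ANCOVA residual variance is σ² − ρ²σ⁴/(σ² + V).

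- Without such children: 0.75 × 4.551 = 3.41.
- In the four scenarios: 3.51, 3.58, 3.79 and 3.95, that is +3%, +5%, +11% and +16%.
- Power for 2.3 mg/L stays at about 99% throughout. For d = 0.778 it is 89%, 88%, 87% and 85%, against 90% without such children.

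**Chance imbalance.** If 6 of 60 children enter this way, a split of 5 to 1 or worse between arms of 30 has probability of about 19%. With r = 5 mg/L, a 5-to-1 split shifts the unadjusted difference in mean change by (5 − 1) × 5/30 = 0.67 mg/L, against a planned 2.3.

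**The case against.** The strongest reply is that the loss is largely a product of assuming unadjusted change scores. Section {20b} mentions control for baseline without restricting it to secondary outcomes. If it covers the primary outcomes, the variance increase shrinks to about 3% to 16%. This stands in part. Nothing in the protocol establishes that the primary analysis is unadjusted, but nothing establishes that it is adjusted either: section {20a} names ANCOVA for the secondary outcomes, and {20b} sits under additional analyses and names no outcome.

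Second, even unadjusted, the planned difference keeps at least 81% power in every scenario shown. The steeper losses appear only for a smaller effect, which is not a planning input. That stands. The smaller effect is still relevant, because the protocol takes its large effect from hs-CRP for want of trials in children with CF and shows no calculation for the other primary markers.

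Third, the share and the rise are assumed, and only hs-CRP is modelled. IL-10 or fecal calprotectin need not behave the same way. Criterion 4 also keeps out children who are still acutely infected. All of this stands. It limits the claim to what may happen, but does not close the gap in the criteria.

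A reader might infer that the gap biases the treatment comparison. The documents do not support that: eligibility is settled before randomised allocation, so such children are expected equally in both arms.

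**Conclusion.** The gap in the criteria is real. The 4-week window depends on hospital admission, criterion 4 has no look-back, and recently treated outpatients may enter before their markers are back to their usual level. The consequence is possible noise and chance imbalance in the primary comparison.

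Its size is uncertain. For shares of 5% to 20% and hs-CRP rises of 3 to 5 mg/L, all of them assumptions, the unadjusted variance of change rises by 9% to 88%, and power for the planned difference falls from 97% to 96% at best and 81% at worst. With baseline adjustment, and a correlation of 0.5 between visits, the loss is minor.

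It would go too far to say that such children do enter with raised markers, or that the trial becomes underpowered for its planned effect. The protocol supplies no data for the first, and the calculation does not show the second. The point is worth acting on because the remedy is cheap and follows the protocol's own rule.

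**What to change.** Reword exclusion criterion 3 so that its existing 4-week window covers any treated pulmonary exacerbation, whether or not the child was admitted. State that such a child is deferred and re-screened rather than excluded for good, and that randomisation and baseline sampling take place only after the window has passed. The protocol already follows this principle for the stool markers: for bacterial overgrowth or parasites found before entry, "Any positive result will be treated with antibiotics before stating the trials".

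The change takes one sentence in the criteria and one screening question, with no extra patients or procedures. The regional clinic and its registry make re-screening practicable. The downside is a delay of usually up to 4 weeks for some children. A few with frequent exacerbations may be deferred repeatedly or not enter at all, which counts for something when recruitment comes from a single clinic.

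Stating in {20a} or {20b} that the baseline adjustment also applies to the primary outcomes would remove most of the remaining loss.
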